With the aforementioned information in mind, there is no doubt that psychological interventions for the treatment of psychological sequelae derived from post COVID-19 condition are urgently needed. The present manuscript describes the study protocol of a multiple baseline n-of-1 trial that aims to study the clinical utility and acceptability of the “Unified Protocol for the Transdiagnostic Treatment of Emotional Disorders” in the treatment of EDs and/or symptoms in a sample of patients with post-COVID-19 condition. Our hypothesis is that a structured UP-based psychological intervention focused on treating emotional dysregulation will be effective in the improvement of EDs and/or symptoms in a sample of patients with post COVID-19 conditions. More precisely, we expect that all outcomes’ measures (i.e., anxiety, depression, emotion dysregulation, quality of life and distress) will significantly improve from pre- to post-assessment. Additionally, we hypothesized that these improvements will be maintained long term (follow-up at one, three, six, and twelve months after the intervention). Finally, our hypothesis is that excellent acceptability (i.e., adherence rates) and satisfaction with the contents and format of the intervention will be found.

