### Design

2.1.

This protocol describes the procedures of a pilot study which uses multiple baseline single case design to explore the preliminary clinical utility and acceptability of the UP in the treatment of EDs or symptoms in a sample of patients with post COVID-19 condition. This trial has been previously registered in clinicaltrials.gov on October 14th, 2022 and updated on January 20th, 2023 (NCT05581277). The present protocol follows the SPENT checklist (SPIRIT extension for N-of-1 trials; Porcino et al., 2020) that can be consulted in Supplementary material A (SPENT checklist) and B (abstract checklist).

Multiple baseline single case design is frequently used in clinical settings to explore the effect of an intervention on a reduced group of patients (Kazdin, 2011). It is selected for this trial as no control group is needed because each participant acts as their own control comparison (Kratochwill et al., 2012). Current guidelines recommend three different baseline conditions with at least 3–5 data points in each group (Kratochwill et al., 2010, 2012). Accordingly, we will assign participants to three different baseline conditions: 6, 8 and 10 days of assessments prior to the beginning of the intervention. Participants will by randomly allocated to one of the three baseline conditions.

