#### Sample size calculation

2.2.2.

In order to stablish the sample size required for this trial, we follow recommendations by Bell et al. (2018) which proposed that a sample size of 60 participants would be adequate considering an effect size of 0.3 and 80% of power. Following this recommendation, our sample will be comprised of 60 participants, 20 in each baseline condition (6, 8 and 10 days of assessment before the intervention).

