### Data analysis

2.6.

The Statistical Package for the Social Sciences (SPSS) version 22.0 for windows (IBM Corp, 2013) will be used to conduct the statistical analysis.

First, normal distribution test will be conducted to explore whether the data obtained followed a normal distribution. According to the distribution of the sample, we will use parametric or non-parametric analyses. Then, descriptive data (mean, standard deviation, and proportions) of all study variables will be reported in order to characterize the sample (i.e., sociodemographic and psychosocial status). Missing-value analysis and the Little Missing Completely At Random test (MCAR) will be used to check whether missing values are randomly presented. Last observation carried forward (LOCF) will be used in this case (Jakobsen et al., 2017).

Analysis of Variance (ANOVA), or its equivalent non-parametric Friedman test, will serve to test whether there are differences between the three baseline conditions at pre-assessment to ensure that randomization resulted in comparable groups. Repeated measures ANOVA will help to determine if between-group (differences in outcome variables between the three baseline conditions at different assessment points) and within group differences (differences between the pre-treatment and the remaining assessments in the outcome variables for each baseline condition) are present. Additionally, effect sizes (Cohen’s *d*) will be calculated for both between and within group analyses. Effect sizes will be interpreted as small (*d* ≈ 0.2), medium (*d* ≈ 0.5) or large (*d* ≈ 0.8).

As recommended for n-of-1 trials, visual analysis of the data by graphs will also be used to determine whether the psychological outcomes improve as a consequence of intervention contents. By doing so, we will establish the baseline pattern on OASIS and ODSIS scales and compare it with the data within the following treatment phase and also with results obtained during the follow-up assessments. The statistical Software R version 4.1.0 (R Core Team, 2021) will be used for the graphical representation of slopes.

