In the present protocol, we describe the procedures for a multiple baseline n-of-1 trial which aims to assess the clinical utility and acceptability of the UP for the transdiagnostic treatment of EDs in a sample of patients with long COVID-19. We hypothesized that the UP will be effective in the improvement of EDs or symptoms and this intervention will be well-accepted by long COVID-19 participants. Specifically, we expect that the UP intervention will help patients to understand the adaptive function of emotions, adopt a non-judgmental attitude toward their unpleasant emotions, practice the cognitive flexibility, overcome avoidance behaviors, and increase their tolerance to physical sensations and unpleasant emotions. As previous literature has shown (Khakpoor et al., 2019; Sakiris and Berle, 2019; Cassiello-Robbins et al., 2020; Carlucci et al., 2021; Schaeuffele et al., 2022; Longley and Gleiser, 2023; Peris-Baquero et al., 2023), we believe that training in these skills may help patients to improve their emotion regulation skills, neuroticism scores and emotion avoidance (transdiagnostic factors) and it may result in a reduction on anxiety and depression symptomatology and an improvement on quality of life. If our hypothesis is confirmed, we would demonstrate that a brief transdiagnostic psychological intervention could be implemented in healthcare systems to alleviate psychological suffering in long COVID-19 patients. Also importantly, results from this trial may support results from previous studies that postulated emotion regulation deficits are relevant in the development and maintenance of EDs (Linehan, 1993; Gratz, 2003). Different scientific studies have highlighted the relevance of emotion regulation in challenging periods as the COVID-19 crisis (Waterschoot et al., 2022) and have claimed the need for delivering interventions that help to develop adaptive emotion regulation strategies (Zhao et al., 2021). Our study could be a first step in this direction.

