Furthermore, results from this study may help to highlight the relevance of maintaining and increasing participants’ quality of life and the usefulness of an adapted UP intervention for this purpose. During the first phases of the COVID-19 crisis, medical efforts were concentrated on stopping the spread of the illness and on improving the survival rate. Two years later, the focus needs to be maintained on contingency measures and severity of symptoms reduction, but we cannot forget that health is not only absence of disease (WHO, 2020) and, consequently, we should also promote good levels of quality of life.

While acknowledging these relevant contributions, the present study has certainly some limitations. First, blinding professionals and participants to baseline conditions is not possible. The same psychological intervention will be applied to all participants irrespective of their baseline condition so we expect that unblended allocation will not affect the trial outcomes. Second, it is important to note that some study characteristics (i.e., eligibility criteria) may limit the generalization of our results to all long COVID-19 populations. In this sense, exclusion criteria may impede some long COVID-19 participants the possibility of participating in this study. Participants currently undergoing psychological or pharmacological treatment cannot participate in this trial. Co-prescribing is one of the most common exclusion criteria in clinical trials for physical conditions (He et al., 2020). In our case, concurrent pharmacological or psychological treatment could interfere with the psychological intervention provided in this trial and it will make it difficult to interpret the results. Finally, participants with low Internet access (i.e., not having Internet connexion or not able to engage in video-calls) will not participate in the intervention as it will be the main channel of communication. Given that in 2022 it was estimated that 93% of Europeans have Internet access (Eurostat, 2017), we expect the impact of this exclusion criteria to be minimal.

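### Pre-to-post change is to be tested separately in each baseline condition (n = 20), although the hypothesis concerns the whole sample and the own-control comparison is made only by eye

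*Protocol article*

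**What the plan says.** **Hypothesis.** The Introduction expects that all outcome measures "will significantly improve from pre- to post-assessment". This is stated for the sample, not by baseline condition.

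**Design and size.** Section 2.1 says that "no control group is needed because each participant acts as their own control comparison". Section 2.2.2 says that "our sample will be comprised of 60 participants, 20 in each baseline condition".

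**Inferential analysis.** Section 2.6 names repeated-measures ANOVA with two targets. One is "differences in outcome variables between the three baseline conditions at different assessment points". The other is "within group differences (differences between the pre-treatment and the remaining assessments in the outcome variables for each baseline condition". The Discussion confirms that "The same psychological intervention will be applied to all participants irrespective of their baseline condition".

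**Analysis of the series.** Section 2.4.2 collects OASIS and ODSIS daily during baseline and weekly during treatment. Section 2.6 compares the baseline pattern with the treatment phase and follow-up by graphs, with R used to draw the slopes. From these graphs the authors intend to judge whether outcomes improve because of the intervention. No test, model or decision rule is named for that comparison.

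**Conclusion foreseen.** The Discussion says: "If our hypothesis is confirmed, we would demonstrate that a brief transdiagnostic psychological intervention could be implemented in healthcare systems".

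**The concern.** Neither stated target of the ANOVA matches the hypothesis. The between-condition comparison sets side by side groups that get identical therapy and differ only in having 6, 8 or 10 days of prior assessment, so it can show whether baseline length matters but not whether the therapy works. The within-condition comparison does address change, but in three groups of 20, and no rule says what to conclude if they disagree.

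The comparison that would justify having no control group is the one between each patient's baseline and treatment phases. It gets no inferential support, yet it carries the causal conclusion. The pre-post tests cannot fill the gap, because they do not separate therapy from natural recovery. Nor do they separate it from regression to the mean, which is plausible because patients can enter on an OASIS or ODSIS cut-off (Table 1).

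At stake are avoidable loss of power, contradictory verdicts that are only chance, and a conclusion firmer than the analysis can bear.

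**Working it through.** **Inputs.** N = 60 and 20 per condition (section 2.2.2). Effect size 0.3 (section 2.2.2, metric not stated); 0.5 and 0.8 are the medium and large benchmarks in section 2.6. Assumed because not stated: two-sided 5% level, d in units of the SD of the change score, no dropout.

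**The plan's own figure.** Section 2.2.2 says that "a sample size of 60 participants would be adequate considering an effect size of 0.3 and 80% of power". A paired t-test at d = 0.3 needs ((1.960 + 0.842)/0.3)² = 87.2, so 88 patients by the normal approximation and 90 by the exact t calculation. The figure of 60 is therefore not reproduced under these assumptions. With level, sidedness and effect metric unstated, that does not prove 60 wrong; it is a separate matter, and what follows does not depend on it.

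**Power of a paired test.** Noncentral t with n − 1 degrees of freedom and noncentrality d√n. At d = 0.5 this is 0.5 × √20 = 2.24 for one condition (critical t = 2.093, 19 df) and 0.5 × √60 = 3.87 pooled (critical t = 2.001, 59 df).

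| d | One condition, n = 20 | Pooled, n = 60 |
|---|---|---|
| 0.3 | 24.7% | 62.8% |
| 0.5 | 56.5% | 96.8% |
| 0.8 | 92.4% | about 100% |

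The smallest effect detectable with 80% power is about 0.66 at n = 20 and 0.37 at n = 60.

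**Agreement of the three verdicts.** With power p in each of three independent conditions sharing the same true effect, all are significant with probability p³, none with (1 − p)³, and verdicts are mixed otherwise.

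- d = 0.3: 0.247³ = 0.015; 0.753³ = 0.427; mixed 1 − 0.015 − 0.427 = 0.558.
- d = 0.5: 0.5645³ = 0.180; 0.4355³ = 0.083; mixed 1 − 0.180 − 0.083 = 0.737 (0.738 before rounding).
- d = 0.8: 0.924³ = 0.789; 0.076³ = 0.0004; mixed 0.211.

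If there were no effect, at least one of three unadjusted tests would be significant with probability 1 − 0.95³ = 14.3%.

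**The series.** Baseline gives 20 × (6 + 8 + 10) = 480 daily scores per scale if complete. Section 2.4.2 changes the recall window to the previous day during baseline, in place of the last week. The treatment-phase scores therefore appear to use the weekly window, and the form changes at the same moment as the phase. Apart from the daily series, Table 2 shows one pre-treatment score, at pre-assessment. The weekly form alone thus gives one point before treatment and no baseline slope.

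**The case against.** **The pooled test is already there.** A repeated-measures ANOVA with condition between and time within also yields a time effect over all 60, with 96.8% power at d = 0.5 on 57 error degrees of freedom. The article does not exclude it. This stands: a reader might infer that groups of 20 are the only possible efficacy test, and the text does not go that far. The power loss arises only if the per-condition comparisons decide the matter. But those are the comparisons section 2.6 spells out, and the pooled term is never named. Taking them as simple effects with pooled error changes little: 59% instead of 56% at d = 0.5.

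**The series is analysed.** A reader might infer that the baseline series is ignored. It is not: section 2.6 compares it with the treatment phase, and the article presents visual analysis as recommended for n-of-1 trials. The point is narrower: graphs alone carry a causal judgement without inference or a decision rule.

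**The between-condition comparison has a use.** It can check that baseline length does not matter, and the article never calls it the efficacy test. One might try to derive an expected difference between conditions from the two to four days of extra waiting. The documents do not support that, because section 2.3 places post-treatment and follow-up assessments after each participant's own completion of the intervention.

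**It is a pilot, and details may sit elsewhere.** Section 2.1 does call the aim preliminary, and model detail is commonly left to an analysis plan. But the per-condition split is stated in the article itself, and the Discussion wording does not keep to the pilot aim.

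**Conclusion.** The concern holds as a mismatch between the hypothesis and the stated analysis, together with an own-control comparison that has no inferential support. Used as written, the per-condition tests have 25% power against 63% pooled at d = 0.3, and 56% against 97% at d = 0.5, with mixed verdicts about 74% of the time in the latter case. These figures rest on the assumed two-sided 5% level, d in SD-of-change units and no dropout; losses would lower both columns. The disagreement figures apply if the three conditions are judged separately, and the article gives no rule for combining them.

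The trial is not unanalysable and its data are not wasted: the same model contains the pooled test, and the series can support more than graphs. This should be settled before the data are analysed. Even the pooled pre-post result will remain uncontrolled evidence.

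**What to change.** 1. Name the pre-to-post time effect pooled over all 60 participants, with baseline condition as a factor, as the primary test for OASIS and for ODSIS. Report each with its 95% confidence interval.
2. Keep the condition and condition-by-time terms only as a check that baseline length does not matter, not as evidence of efficacy.
3. Supplement the graphs with an inferential phase comparison of the daily and weekly series, for example a multilevel model or a randomisation test that uses the randomised baseline lengths. State that the recall window changes between phases, so a level shift at treatment start is confounded with the form unless the forms are aligned. Restricting the model to one form does not solve this, since the weekly form leaves no baseline slope.
4. Describe the pre-post result as preliminary and uncontrolled, in line with the pilot aim in section 2.1, and reword the Discussion sentence on what a confirmed hypothesis would show.

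**Cost.** Items 1, 2 and 4 are wording. Item 3 is modest extra programming in R, which is already named, and needs no new data unless the sponsor chooses to align the forms. The downsides to report are imprecise baseline slopes from 6 to 10 days and the recall-window limitation.

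### The hypothesis that gains are maintained is paired with contrasts against pre-treatment, which do not test whether the post-treatment gain was kept

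*Protocol article*

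**What the plan says.** The Introduction states two separate hypotheses. The first is that the outcome measures "will significantly improve from pre- to post-assessment". The second concerns what happens afterwards: "we hypothesized that these improvements will be maintained long term (follow-up at one, three, six, and twelve months after the intervention").

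The Data analysis section (2.6) plans repeated measures ANOVA. Its within-group part is defined as "differences between the pre-treatment and the remaining assessments in the outcome variables", taken separately for each baseline condition. Its between-group part compares the three baseline conditions with one another at the assessment points. Cohen's d accompanies both parts, read against benchmarks of 0.2, 0.5 and 0.8. The visual analysis covers OASIS and ODSIS only. It takes the baseline pattern as its reference and will "compare it with the data within the following treatment phase and also with results obtained during the follow-up assessments".

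On numbers, the Sample size calculation section (2.2.2) says "our sample will be comprised of 60 participants, 20 in each baseline condition".

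No stated analysis compares a follow-up with the post-assessment, and no criterion is given for calling a gain maintained.

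**The concern.** The improvements in the second hypothesis are the pre-to-post gains of the first. Maintenance is therefore a statement about change between post-assessment and each follow-up. A contrast that starts at pre-treatment adds two changes together: the gain during therapy and whatever happened afterwards. A large early gain can carry the sum to significance even when much of it has since been lost. In a small group, the sum can miss significance even when nothing was lost. Neither result answers the question asked.

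This does not rest on the article being silent. The article names its contrast, and that contrast answers a different question. At stake is the second hypothesis. The pre-to-post question is unaffected.

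**Working it through.** **Inputs from the protocol.** 60 participants in total, 20 per baseline condition (section 2.2.2); within-group contrasts anchored at pre-treatment, per condition (section 2.6); d = 0.8 as the benchmark for a large effect (section 2.6).

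**Assumptions, not in the protocol.** Two-sided alpha 0.05; equal SD at each time; correlation ρ between any two times from 0.3 to 0.7; half of the gain lost by follow-up; paired t-test with no dropout. The 0.8 SD gain borrows the benchmark and is not a forecast made by the protocol.

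**The plan's own figure.** The protocol cites a recommendation that "a sample size of 60 participants would be adequate considering an effect size of 0.3 and 80% of power". It does not state the metric, test, alpha or correlation. A paired test with a standardised mean change of 0.3 needs 90 participants (two-sided, exact t). If 0.3 is a difference in units of the raw SD, the need is 90 at ρ = 0.5 and 55 at ρ = 0.7. The figure of 60 can therefore be neither reproduced nor refuted, and nothing below depends on it.

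**Step 1. What the planned contrast estimates.** Let G be the pre-to-post gain and L the loss after post.
- Pre versus follow-up estimates G − L.
- Maintenance concerns L.
- With G = 0.8 and L = 0.4, the planned contrast has expected value 0.4 SD. A person who gained 0.4 SD and kept all of it has the same value. The contrast cannot tell the two apart.

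**Step 2. How often pre versus follow-up is significant when half the gain is lost.** The standardised mean change is dz = (G/2)/√(2(1−ρ)), and power comes from the noncentral t with n−1 degrees of freedom. For G = 0.8 and ρ = 0.5, dz = 0.4/√1 = 0.40.

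| Initial gain | ρ | dz | n = 60 pooled | n = 20 per condition |
|---|---|---|---|---|
| 0.8 SD | 0.3 | 0.338 | 73% | 30% |
| 0.8 SD | 0.5 | 0.400 | 86% | 40% |
| 0.8 SD | 0.7 | 0.516 | 98% | 59% |
| 0.5 SD | 0.5 | 0.250 | 48% | 19% |
| 0.3 SD | 0.5 | 0.150 | 21% | 10% |

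A simulation of 10,000 trials with G = 0.8 and ρ = 0.5 agrees: 86% at n = 60 and 40% at n = 20. At n = 60, 73% of those trials had both a significant benefit over pre-treatment and a significant loss since post. The planned contrasts would report only the first.

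**Step 3. Low power when nothing is lost.** With a gain of 0.5 SD fully kept and ρ = 0.5, pre versus follow-up at n = 20 is significant in only 57% of trials. Non-significance in one condition would not show relapse.

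**Step 4. Precision of the missing contrast.** The SD of post-to-follow-up change is √(2(1−ρ)), and the 95% CI half-width is t × √(2(1−ρ))/√n, with t = 2.001 at n = 60 and 2.093 at n = 20.

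| ρ | n = 60 | n = 20 |
|---|---|---|
| 0.3 | 0.31 SD | 0.55 SD |
| 0.4 | 0.28 SD | 0.51 SD |
| 0.5 | 0.26 SD | 0.47 SD |
| 0.6 | 0.23 SD | 0.42 SD |
| 0.7 | 0.20 SD | 0.36 SD |

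Take, only as an illustration, a loss margin of 0.4 SD (half of 0.8). At n = 60 every half-width is below it. At n = 20 it is exceeded for every ρ shown except 0.7. With no true loss, ρ = 0.5, one-sided 0.025 and 80% power, that margin needs ((1.96 + 0.84)/0.4)² ≈ 49, about 50 participants. The pooled sample covers this before dropout; a single condition does not.

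**The case against.** Four points can be made for the plan.

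1. **No confirmation rule is written.** A reader might infer that a significant pre-versus-follow-up result would be taken as proof of maintenance. The protocol does not say so; the ANOVA is only said to help determine whether differences are present. This stands. The defect is that no stated analysis addresses the hypothesis, not that a wrong rule is laid down.

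2. **The contrast does not reliably stay significant after relapse.** A reader might infer that losing half the benefit would leave the result significant. That is likely only for a large initial gain with all 60 pooled. The protocol runs the contrast per condition, where it is significant less than half the time at a 0.8 SD gain and ρ = 0.5, and far less often at smaller gains. This also stands: the contrast can stay significant, and no more than that.

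3. **Relapse would not be hidden.** Pre-to-post and pre-to-12-month Cohen's d would both be reported. In the illustration they fall from 0.8 to 0.4, and the OASIS and ODSIS graphs extend to follow-up. This stands in part. These are descriptive and anchored at pre-treatment or baseline, and none estimates the loss after post-assessment with an interval.

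4. **It is a pilot, and an analysis plan not shown may add pairwise comparisons.** Possible. But the article states maintenance as a hypothesis and names its within-group contrast explicitly, so the mismatch is in the published text.

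**Conclusion.** The concern holds in this form: a stated hypothesis is paired with a stated contrast that does not test it. That mismatch is structural and does not depend on effect size, correlation or alpha. Its practical size does. For a 0.8 SD gain half lost, a result that looks favourable occurs with probability 73–98% if all 60 are pooled and 30–59% at 20 per condition (ρ 0.3–0.7). For an initial gain of 0.3 SD it is about 21% and 10% (ρ = 0.5). These figures are illustrations, since the protocol gives neither the expected gain nor the correlation. The change should be made, but the pre-to-post hypothesis stands without it.

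**What to change.** - From the same repeated-measures model, pooled over the three baseline conditions, add the post-to-follow-up contrast with a 95% CI at each follow-up for OASIS and ODSIS. Name 12 months as the main one.
- Set in advance the largest loss still compatible with calling a gain maintained, and make that statement only if the interval excludes it. The margin is for the sponsor to choose and justify; half of the pre-to-post gain is used above only as an example.
- Describe pre-versus-follow-up results as still improved compared with pre, and nothing more.
- Do not run the maintenance contrast per condition, because the intervals at n = 20 are too wide.
- Repeat the contrast without carried-forward values. Section 2.6 names last observation carried forward. For anyone last seen at post-assessment, that method sets the later change to zero and so mimics maintenance.

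The cost is one extra contrast and one pre-set margin. All the scores are already scheduled in Table 2, so no new data are needed. The price is that a maintenance claim becomes harder to make, and dropout will widen the interval beyond the figures given for 60.
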